**Fig. 2 Fig2:**
[figure not shown]
Overview of visits, assessments, and interventions

### Sample size {14}

To reach a power of 80% (*α* = 0.05, *β* = 0.2) for detecting a between-groups effect of CBT-I on ISI of 4, follow-up data on 24 patients in each group is needed. Since an attrition rate of around 25% is expected, the aim will be to include a total of 60 patients. For the power calculation, means and standard deviations from a previous study were used [20]. However, the between-groups effect is expected to be less since we are using two active interventions.

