## Trial status

Protocol version 1.5, 11th June 2025.

Recruitment began 28th November 2024 and will be completed approx. 31^st^ December 2026.

As per January 12, 2026, 10 patients have been screened, 5 patients have been included, and 3 patients have completed the trial.

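### Sixty patients at the expected 25% attrition leave 45 with follow-up, not the 48 that the sample-size statement needs for 80% power; 64 would be required

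*Protocol article*

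**What the plan says.** The Sample size section {14} sets 80% power at α = 0.05 for "detecting a between-groups effect of CBT-I on ISI of 4" and states that "follow-up data on 24 patients in each group is needed". With 1:1 allocation (Trial design {8}) that is 48 patients. The next sentence gives the recruitment target: "Since an attrition rate of around 25% is expected, the aim will be to include a total of 60 patients".

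On inputs, the section says "For the power calculation, means and standard deviations from a previous study were used [20"; it prints neither the standard deviation (SD) nor whether the test is one- or two-sided. It closes with the remark that "the between-groups effect is expected to be less since we are using two active interventions".

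The Trial status section gives a recruitment period from 28 November 2024 to approximately 31 December 2026 and reports: "As per January 12, 2026, 10 patients have been screened, 5 patients have been included, and 3 patients have completed the trial".

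**The concern.** The requirement of 48, the attrition of 25% and the total of 60 are printed together and are inconsistent. The total appears to have been obtained by adding 25% to the number needed, when the number needed should have been divided by the proportion expected to remain. If attrition is as expected, the trial reaches its full target and still has fewer patients with primary-outcome data than its own power statement requires.

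Two neighbouring points bear on how that power statement is read. The closing remark about a smaller effect names no comparator, so it is unclear whether 80% is the power at the effect the investigators expect. The accrual reported under Trial status also makes it doubtful that 60 will be reached by the stated date. If the trial ends well short, a non-significant result would say little about whether CBT-I is better than CBT for insomnia.

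**Working it through.** **Inputs.** From Sample size {14}: 24 per group with follow-up (48 in total), difference 4 ISI points, α = 0.05, power 80%, attrition about 25%, total 60. From Trial design {8}: 1:1 allocation. From Trial status: 28 November 2024 to 12 January 2026 is 410 days; to 31 December 2026 is 763 days; 5 included.

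**Step 1: reproduce the printed total.**
- 48 × (1 + 0.25) = 60. This matches the plan.
- 48 / (1 − 0.25) = 64, or 32 per group. This is the number that leaves 48 after a 25% loss.

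**Step 2: what 60 delivers.**

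| Attrition | Evaluable from 60 | Needed for 48 evaluable |
|---|---|---|
| 20% | 48.0 | 60 |
| 22% | 46.8 | 62 |
| 25% | 45.0 | 64 |
| 28% | 43.2 | 67 |
| 30% | 42.0 | 69 |

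The break-even attrition is 1 − 48/60 = 20%.

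**Step 3: the SD implied by the plan.** No SD is printed, so it is solved from 24 per group, a difference of 4 and 80% power in a two-sample t-test.
- Two-sided: standardised effect 0.826, SD = 4 / 0.826 = 4.84 (4.95 by the normal approximation).
- One-sided: standardised effect 0.729, SD = 4 / 0.729 = 5.49.

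**Step 4: power for 4 points with 45 evaluable (22.5 per group).**
- Two-sided, SD 4.84: 77.3% (normal approximation 77.4%).
- One-sided, SD 5.49: 77.6%.

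The unstated SD and sidedness therefore hardly matter here, because each SD is calibrated to give 80% at 24 per group. The loss is 2 to 3 percentage points.

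**Step 5: the remark about a smaller effect.** Two readings are possible.
- (a) The 4 points come directly from the earlier study and the expected effect is below 4. The 80% is then not the power at the expected effect. The document does not give that effect. Purely as illustration, with 45 evaluable, SD 4.84 and a two-sided test, power is 66% at 3.5 points, 53% at 3 and 27% at 2.
- (b) The earlier study's effect was larger and 4 is already the reduced value. The remark then takes nothing from the power.

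The text does not decide between them.

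**Step 6: accrual (feasibility, separate from the arithmetic above).**
- Elapsed share of the window: 410 / 763 = 54%.
- Observed rate: 5 / 410 × 30.44 = 0.37 per month.
- Constant-rate projection: 5 + 353 × 5/410 = 9.3 by 31 December 2026. A gamma-Poisson 95% predictive range is about 5 to 17 (prior shape 0.5; other weak priors move a limit by about one patient).
- Rate needed to reach 60: 55 / 353 × 30.44 = 4.7 per month, about 13 times the observed rate.
- If 17 were randomised, the top of that range, and 25% lost, 12.75 would be evaluable. Two-sided power for 4 points would be about 27% and the 95% confidence interval about ±6 points. With 9 randomised the same calculation gives about 14% and ±10 points.

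**The case against.** The best defence is that the attrition figure is a rounded forecast. At 20% the total of 60 is exactly right, and at 22% power is still 79%. It stands that the consequence is small. It does not stand that the text is consistent: the section names 25%, and at that value 60 leaves 45. Carrying the last observation forward, as the missing-data section {20c} proposes, does not restore the count either, since the sample-size section asks for follow-up data on 24 per group.

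A reader might infer from "However, the between-groups effect is expected to be less since we are using two active interventions" that the plan concedes it is underpowered. The documents do not support that. The remark follows a sentence about an earlier study, and 4 points may already be the reduced target. The powers at 3.5, 3 and 2 points use effects that appear nowhere in the protocol.

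A reader might also take the accrual figures as a further error, or as showing that the trial will end with about 9 patients. Neither follows. Trial status is a dated report that contains no miscalculation, the end date is approximate, the steering committee reviews inclusion every third month, and a projection from five inclusions is imprecise. What stands is that even the upper end of the projection is under a third of the target.

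Finally, nothing in the protocol says that a null result would be read as no difference. The trial is declared a superiority trial, and the dissemination plan treats inconclusive results as a category of their own.

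**Conclusion.** The point holds as an internal inconsistency of modest size. At the attrition the plan itself expects, 60 patients yield 45 with follow-up, 3 short of the 48 required, and 64 would be needed. Power for a 4-point difference is then about 77%, not 80%. The count of 45 rests only on printed numbers. The 77% rests on an SD back-calculated from the plan's inputs (4.84 two-sided, 5.49 one-sided) and a two-sample comparison of means.

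The remark about a smaller effect is an ambiguity to be cleared up; it does not establish a further loss of power. The accrual is a feasibility concern: at a constant rate about 9 patients (range about 5 to 17) would be included by the approximate end date, so the target of 60 and that date cannot both stand without a large change in recruitment.

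**What to change.** In Sample size {14}:
- Either keep 60 and state that 25% attrition leaves 45 evaluable patients and about 77% power for 4 points, or state that 64 must be included for 48 evaluable.
- State whether the 4 points are before or after the reduction expected from using two active interventions. If before, give the power at the smaller expected effect.
- Print the SD and the sidedness with the calculation, so that the 77% can be confirmed.

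Separately, as a feasibility note, acknowledge beside the Trial status figures that the target and the end date are in tension, and say which is expected to change. State now, before any comparison between arms, that if the target is missed the primary result will be reported as an estimate with its 95% confidence interval and will not be interpreted as showing no difference.

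The cost is a few sentences. Keeping 60 requires no extra patients; the stated power becomes slightly less favourable. Choosing 64 adds four patients to a target that is already hard to reach.

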### Recruitment {15}

Leading up to and during the recruitment period, UCS will promote participation in the study internally in the Capital Region Mental Health Services, primarily through posters in the waiting areas of outpatient clinics and short lectures about the project to relevant clinicians. Further, complex schizophrenia patients referred for second opinion at UCS will be offered additional information on participation if they fit the target group.

## Assignment of interventions: allocation

### Sequence generation {16a}

The allocation sequence used is computer-generated using an online allocation tool (https://www.sealedenvelope.com/). This allows for randomization to be done with variable block sizes (2, 4, and 6) to achieve equal sample size in the two different groups over time.

### Concealment mechanism {16b}

The randomization process is concealed using opaque, sealed, and sequentially numbered envelopes. This concealment mechanism is done without the participation of those responsible for enrolling patients. Further, the envelopes are stored in a location unbeknownst to those enrolling patients. Patients will be given the next envelope in the sequence, which contains the intervention they are assigned to. The allocation process will take place in a separate room without the participation of those in charge of enrolling patients.

### Implementation {16c}

The allocation sequence is generated using the above online tool by an academic employee at UCS, who is not otherwise an active part of the study, apart from aiding with creating figures and tables for the article. The enrollment of participants is done by one psychologist ([name]) and one nurse, who will manage the process from the first contact until assigning of intervention. The same academic employee will manage the process of assigning participants to the interventions.

## Assignment of interventions: blinding

### Who will be blinded {17a}

Most of the study will be unblinded. However, to ensure valid and unblinded rating of psychopathology, the PANSS interviews will be videotaped and rated by external raters.

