### Trial design {8}

This is a 12-week non-blinded randomized controlled trial (RCT) with a superiority framework. Patients will be randomized 1:1 using a block randomization regimen with variable block sizes (2, 4, and 6), which is done to achieve equal sample size in different groups over time [30]. For a flowchart of the trial, see Fig. 1.

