### Outcomes {12}

The primary outcome is improvement of the individual ISI score after 12 weeks. Secondary outcome measures are ISI score after 24 weeks and changes in PANSS (both total and subscale scores) [44], Global Assessment of Functioning (GAF) [45], WHO Well-Being Index (WHO-5) [46], Functioning Assessment Short Test (FAST) [47], Personal and Social Performance Scale (PSP) [48], the Process of Recovery Questionnaire (QPR) [49], the Treatment Expectation Questionnaire (TEX-Q) [50] and PSG. All outcomes are measured at baseline, after 12 weeks, and at 24 weeks, except for PSG, which is only measured at baseline and after 12 weeks.

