### Procedure for unblinding if needed {17b}

Not applicable, no blinding planned for the intervention of the study.

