
For PANSS, PSP and GAF, ongoing training of assessors is already implemented through co-rating at a weekly to monthly frequency.

An overview of the data collection plan at baseline and follow-up is provided in Fig. 2.

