### Confidentiality {27}

The project will comply with the data protection regulation and data protection act (Databeskyttelseslov- og forordning). The project has been approved by the Danish Data Protection Agency under the common Capital Region Mental Health Services’ umbrella application. All data on a secured data-drive (REDCap). REDCap is a secure, web-based software platform designed to support data capture for research studies [60]. Data extracted for analyses will be handled as confidential data and pseudo-anonymized using project letters and ID numbers, which will be kept at closed, secured, and monitored data-drives. PSG data will likewise be kept in pseudo-anonymized form in a secured data folder. Only anonymized data will be published.

The data will be stored in REDCap until 31 December 2039. Subsequently, the data will be archived in fully anonymized form.

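### External rating is planned for PANSS only: GAF, PSP and FAST fall under the unblinded default, and nobody is named as scoring the PSG or said to be masked

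*Protocol article*

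**What the plan says.** The trial design section {8} reads "This is a 12-week non-blinded randomized controlled trial (RCT) with a superiority framework". Section {17a} repeats the default, "Most of the study will be unblinded", and then takes out one measure: "the PANSS interviews will be videotaped and rated by external raters". The stated purpose of that exception is "to ensure valid and unblinded rating of psychopathology". Section {17b} adds "Not applicable, no blinding planned for the intervention of the study".

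The outcomes section {12} lists GAF, PSP and FAST as secondary outcomes at 12 and 24 weeks, and PSG at 12 weeks. Section {18a} describes GAF as a rating instrument, PSP as a semi-structured interview and FAST as a short interview. On the quality of rating it says: "For PANSS, PSP and GAF, ongoing training of assessors is already implemented through co-rating at a weekly to monthly frequency". The fourth hypothesis under Objectives {7} expects an objective improvement on PSG in sleep latency, wake after sleep onset, sleep efficiency and total sleep time. On the recordings, the confidentiality section {27} says: "PSG data will likewise be kept in pseudo-anonymized form in a secured data folder". The article does not say who scores them.

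**The concern.** The plan accepts that an interview-based rating in an open trial benefits from an independent rater, and provides one for PANSS. The same reasoning applies to GAF, PSP and FAST, which also turn an interview or clinical impression into a score. Co-rating brings assessors into agreement, but it does not keep the arm from them. PSG staging is a reading step too, and it carries a named hypothesis as the objective evidence.

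What is at stake is how the secondary results can be read. A difference on a scale rated with knowledge of the arm may reflect the patient or the rater, and the data cannot separate the two. The statistical methods section {20a} applies no multiplicity correction to the secondary outcomes, so nothing later in the plan would temper a signal produced by the raters.

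**Working it through.** **1. Which outcomes the PANSS exception leaves out**

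| Outcome | Who produces the score ({18a}) | Masking stated |
|---|---|---|
| ISI (primary), WHO-5 | patient self-report | none; rater masking does not apply |
| PANSS | interviewer, with external rating from video | external raters named; masking to arm not stated |
| GAF | assessor rating | none; falls under the default |
| PSP | assessor interview | none; falls under the default |
| FAST | assessor interview | none; falls under the default |
| PSG | scorer not identified | none; not listed as an exception |

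**2. Whether the PANSS exception amounts to masking.** As printed, {17a} says "to ensure valid and unblinded rating of psychopathology". This may be a slip for blinded. Nothing else in the article says that the external raters do not know the arm, so handing them more scales would not by itself produce masking.

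**3. Count of contrasts.** From {7} and {12}, assuming one contrast per score and follow-up visit:
- ISI at week 24: 1
- PANSS total and three subscales × 2 visits: 8
- GAF, WHO-5, FAST, PSP, QPR and TEX-Q × 2 visits: 12
- four PSG measures at week 12: 4

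The total is 1 + 8 + 12 + 4 = 25. GAF, PSP and FAST account for 3 × 2 = 6 of them. The four PSG contrasts are a separate group, because the scorer is unknown.

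**4. Illustration for the rated scales.** The plan gives no figure on rater bias, so there is none to reproduce. Inputs: 24 per arm with follow-up data (sample size section {14}), two-sided α = 0.05 (sidedness assumed), and no true difference. A pure rating shift of b SD between arms is an assumption.

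Noncentrality = b × √(24/2) = 3.464b; degrees of freedom = 46; critical value = 2.013. The false-positive rate is P(|T| > 2.013), where T is noncentral t.

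| Assumed shift b | Noncentrality | False-positive rate |
|---|---|---|
| 0 | 0 | 5.0% |
| 0.2 SD | 0.693 | 10.4% |
| 0.3 SD | 1.039 | 17.4% |
| 0.4 SD | 1.386 | 27.4% |

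The rates apply per contrast and are the same whichever arm the shift favours. Nothing in the article supports a shift of this size for PSG, so they are not carried over to it.

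**The case against.** **The open design is disclosed.** Sections {8}, {17a} and {17b} say so plainly, and masking is not falsely claimed for these scales. That stands. The point concerns a design choice that can be improved, not a contradiction. Section {17b} speaks only of the intervention, so it does not rule out masked assessors.

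**The outcomes are peripheral.** None of the four hypotheses uses GAF, PSP or FAST, the secondary analyses are declared exploratory, and masking raters cannot protect a self-reported ISI. This stands and limits the weight of the point. PSG is different, since the fourth hypothesis rests on it.

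A reader might infer four stronger things that the article does not support:

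- *That PSG is scored by unblinded staff.* No scorer is named, the default covers most of the study rather than all of it, and a condensed article may leave the scoring procedure to the full protocol. What can be said is that PSG is not among the stated exceptions.
- *That the function scales are biased towards CBT-I.* The intervention description {11a} gives the control therapy psychopathology and functional difficulties as its target. A rater who knows the arm could as well expect the control arm to do better on function, so the direction is unknown.
- *That the co-rating sentence shows in-house assessors who know the allocation.* It covers PANSS as well, which is externally rated, and omits FAST. It does not settle who rates the trial outcomes or what they know.
- *That masking everything is almost free.* The consent section {26a} tells patients about recording one therapy session and the psychopathology assessments only. Recording PSP and FAST would go beyond that, and nothing shows that a PANSS video holds enough to rate GAF.

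**Conclusion.** The concern holds in limited form. By a stated choice, three assessor-rated secondary outcomes (6 of about 25 secondary contrasts) have no independent or masked rating and are open to rater bias of unknown direction. PSG adds 4 contrasts for which the scorer, and what the scorer knows, are not stated. The one exception, PANSS, is not described as masked.

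The false-positive rates of about 10%, 17% and 27% show what assumed shifts of 0.2, 0.3 and 0.4 SD would do to a rated scale. They do not estimate the bias in this trial. The primary analysis is unaffected. The change is worth making because its main parts cost little and recruitment is at an early stage: the trial status section reports 5 patients included of 60 planned.

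**What to change.** Amend {17a} to name, for each assessor-dependent outcome, who scores it and whether they know the arm:

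- **PSG.** Score from the pseudonymised files with arm and visit removed and in mixed order, by a scorer not told the allocation. This is free, and can also be applied to recordings already stored.
- **PANSS and GAF.** State that the external raters are masked to arm, and to visit where feasible, and correct the printed wording accordingly. Have them also rate GAF from the existing video if it contains enough on functioning. This costs a few minutes per video.
- **PSP and FAST.** Where available, use an existing assessor who treats no trial patient and is not told the arm. Alternatively, record these interviews after amending the patient information. If neither is possible, report these scales as rated unmasked.

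The downside is slightly more rating time. If PSP and FAST are recorded, the patient information must also be amended, and section {25} has such changes approved by the ethics committee.

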### Procedure for unblinding if needed {17b}

Not applicable, no blinding planned for the intervention of the study.

## Data collection and management

### Plans for assessment and collection of outcomes {18a}

#### Assessment and collection of data

The following instruments will be implemented in the study:ISI is a brief seven-item questionnaire designed to measure perceived as well as changes in levels of insomnia, which has been thoroughly validated [25]. It includes items pertaining to nighttime impairment, such as trouble getting to sleep, staying asleep, and early morning awakenings, and daytime impairment, such as satisfaction, daily functioning, noticeability, and worries related to sleep patterns. Internal reliability, as measured by Cronbach’s coefficient alpha, ranged from 0.76 to 0.78 at baseline and follow-up evaluation. Concurrent validity, as measured by Pearson’s *r* coefficient, ranged from 0.07 to 0.91 across several information sources at baseline and follow-up. These results generally show a significant correspondence between patients’ self-perceived insomnia severity and that obtained from significant others and clinicians [25].PANNS is a semi-structured interview based on 30 items developed to assess the positive, negative, and general psychopathological symptoms of patients suffering from schizophrenia [44]. It has been extensively used in both clinical and research settings to measure and monitor the development of symptoms in schizophrenia. Internal reliability, as measured by Cronbach’s coefficient alpha, was 0.73, 0.83, and 0.79 for the Positive Scale, Negative Scale, and General Psychopathology Scale, respectively. Criterion-related validity (composed of discriminant and convergent validity), as measured by Pearson’s *r* coefficient, generally showed that the subscales of PANSS tend to correlate positively with related constructs and negatively with unrelated constructs. An overview of correlations can be seen in Kay et al. [44].GAF is a transdiagnostic rating instrument developed for objectively assessing the severity of psychiatric illness as it relates to the level of psychological, social, and occupational functioning [45]. This is rated in a single score ranging from 0 to 100 in 10-point intervals, which makes GAF an easy and quick tool to assess the level of functioning. GAF has shown high inter-rater reliability of 0.88 [48].PSP is a semi-structured interview developed to assess functioning in four separate dimensions for patients suffering from schizophrenia [48]. The four dimensions are socially useful activities, personal and social relationships, self-care, and disturbing and aggressive behaviors. This makes PSP a more in-depth instrument for assessing the level of functioning, which is an important variable in schizophrenia research. Inter-rater reliability for this instrument ranged from 0.68 to 0.90 across different occupations, professional backgrounds, and numbers of years working in mental health care [48].FAST is a 24-item instrument administered as a short interview designed to assess challenges in daily functioning in psychiatric patients, which is centered around six domains: autonomy, occupational functioning, cognitive functioning, financial issues, interpersonal relationships, and leisure time [47]. FAST has been demonstrated to have excellent internal consistency (Cronbach’s alpha = 0.89) and concurrent validity through a moderate positive correlation with the Brief Psychiatric Rating Scale and a strong negative correlation with the GAF scale [51].WHO-5 is a brief 5-item self-report measure used to assess levels of subjective psychological well-being, which is one of the most widely used questionnaires in this area [46]. Across several samples, WHO-5 has been shown to have excellent internal consistency with Cronbach’s alpha ranging from 0.83 to 0.95 [52]. Furthermore, WHO-5 has robust enough validity to warrant use as a well-being rating scale in clinical trials [46].QPR is an instrument used to assess the concept of recovery in psychiatric patients recovering from psychosis, which consists of two subscales, namely intrapersonal and interpersonal [49]. The revised version used in the present study is a 15-item instrument, which has been shown to have excellent internal consistency at a Cronbach’s alpha of 0.89 and a convergent validity at a Pearson’s *r* of 0.73 [53].TEX-Q is a 15-item generic instrument to assess treatment expectations in a multidimensional manner [50]. The overall scale has shown good internal consistency at Cronbach’s alpha = 0.79 with the subscales ranging from 0.71 to 0.91, while the test-retest reliability (as measured by Pearson’s *r*) was high for the overall scale (Pearson’s *r* = 0.76, *p* < 0.001) and ranging from *r *= 0.60 to 0.84, *p* < 0.001 for the subscales, except for the process subscale (*r* = 0.39, *p* = 0.026) [50].PSG is a comprehensive overnight sleep study that records multiple physiological parameters, including brain activity, eye movements, respiratory effort, airflow, and oxygen saturation [27, 54]. It measures sleep stages, breathing patterns, and limb movements to diagnose and evaluate sleep disorders such as sleep apnea, narcolepsy, and parasomnias [55]. In research, PSG is the gold standard for assessing sleep architecture and treatment outcomes. PSG demonstrates high validity and test-retest reliability for key sleep parameters, especially in controlled laboratory settings [56].

For PANSS, PSP and GAF, ongoing training of assessors is already implemented through co-rating at a weekly to monthly frequency.

An overview of the data collection plan at baseline and follow-up is provided in Fig. 2.

